### Safety Monitoring

Both internal and external monitoring is utilized through this study. The principal investigator has on-site assessment through monthly meetings with the supervisors at both hospitals. An external person is also appointed at each research site to independently monitor the research process.

### Statistical Analysis

All statistical analysis will be done using Statistical Package for the Social Sciences (SPSS) Research Engine, Version 22.0 IBM SPSS Statistics (2015). We plan to employ the Student *t* test to compare mean outcomes in each group when assuming a normal underlying distribution can be justified and the Mann-Whitney U test to compare medians when this assumption fails. We will compare differences in proportionate outcomes using a Chi-square analysis. When calculating multiple time points for the purpose of comparing groups over time, we will apply appropriate correction for multiple testing using the Bonferroni correction. For all of these methods, we will determine if there is a statistically significant difference between the groups (*P* values less than .05). Results will be presented as differences between groups with 95% confidence intervals. We will also consider both analysis of covariance (parametric) or Kruskal-Wallis (non-parametric) testing as appropriate and will investigate the influence of potential confounders and correlations by logistic or multiple regression techniques. Further, we will randomly select two groups of patients (30 delirium-positive and 30 delirium-negative) to cross validate our results and assess whether they are stable for both samples.

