## Methods

We are conducting a prospective case-control study in two ICUs in Australia: the Canberra Hospital in the Australian Capital Territory and the Prince of Wales Hospital in Sydney, New South Wales. The study was approved by the ACT Health Human Research Ethics Committee (ETH.6.12.130) and the Southern Health Human Research Committee (12/242 (HREC/I2/POWH/460). Since eligible participants are not able to give informed consent on enrolment due to their health status (ICU treatment), their substitute decision maker or “person responsible” will be identified. This person is approached to provisionally consent to participation on behalf of the patient. The “person responsible” is given a full explanation of the study and is provided with the Cognitive and Psychosocial Assessment (CAPA) study information sheet. They are then asked to consent to participate in the study on behalf of themselves and the patient. If the patient is not sedated or delirious, the study is explained to them; however, the “person responsible” is still required to complete and sign the consent form on behalf of themselves and the patient whilst the patient is ventilated. Further, consent from the “person responsible” authorizes their later involved in the assessment of patients’ overall function at the 12-month follow-up.

Despite being recruited to the study through their “person responsible,” the patients receive no other intervention other than standard protocol care during their ICU stay. The standard care in both recruiting sites involves administering the following during mechanical ventilation: (1) the Richmond Agitation and Sedation Score (RASS) [26,27], and (2) the Confusion Assessment Method for the ICU (CAM-ICU) [28].

After being recruited to the study, the patients have their sedation level assessed by the RASS [26,27] every 4 hours. The RASS is a scale that indicates the patient’s level of sedation and ranges from +4 to –5. A RASS score of 0 represents a patient who is alert and calm, while positive scores indicate different levels of agitation from restless (+1) to combative (+4). Negative scores indicate different levels of drowsiness from drowsy (–1) to unarousable (–5).

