### Sample Size

The primary outcome of this study is the relative decrement in MMSE at 6 months after discharge from the ICU. We used the most relevant clinical trial employing MMSE to quantify cognitive function of both delirium-positive and delirium-negative patients to estimate the expected outcomes for our patients at 6 months after discharge from the ICU in order to make a sample size calculation. We estimated the clinically important reductions expected in MMSE and calculated that, at a type 1 error rate of 5% (alpha .05), we can find the clinically significant difference of 2 points on the MMSE between groups with 80% power if we include a minimum of 81 patients in each group (delirious and not delirious). To allow for potential dropouts following recruitment, we plan to enroll 200 patients.

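### The committed group comparisons pool two ICUs with tests that cannot hold site, so a between-site difference can enter the delirium contrast

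*Protocol article*

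**What the plan says.** All references are to the protocol article.

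- **Design (Methods):** "We are conducting a prospective case-control study in two ICUs in Australia", one in Canberra and one in Sydney.
- **Exposure (Methods):** delirium status is observed, not assigned. "The standard care in both recruiting sites involves administering the following during mechanical ventilation", followed by RASS and CAM-ICU. CAM-ICU is given only when RASS lies between –2 and +3, and any positive result puts the patient in the delirium-positive group.
- **Group comparisons (Statistical Analysis):** for continuous outcomes, a Student *t* "test to compare mean outcomes in each group when assuming a normal underlying distribution can be justified and the Mann-Whitney U test" when normality fails. For binary outcomes: "We will compare differences in proportionate outcomes using a Chi-square analysis".
- **Further analyses (same section):** ANCOVA or Kruskal-Wallis will be considered as appropriate, and the influence of potential confounders will be examined by logistic or multiple regression. No covariate is named.
- **Sample Size:** "we can find the clinically significant difference of 2 points on the MMSE between groups with 80% power", with "a minimum of 81 patients in each group (delirious and not delirious").

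Site is not named as a covariate, stratum or confounder anywhere in the analysis text.

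**The concern.** No randomisation balances delirium status between the hospitals. The label is generated inside each ICU: sedation depth decides who can be tested with CAM-ICU, and routine testing decides who is labelled. The proportion labelled delirious may therefore differ between the units. Outcome levels may differ too, through case mix or care.

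The tests that the plan commits to treat all patients as if they came from one unit. If the ICU with more delirium also has worse outcomes, the pooled contrast mixes a hospital difference with the delirium difference. The non-parametric route has no way round this in the named tests, because neither Mann-Whitney nor Kruskal-Wallis takes a covariate. At stake is whether the estimate can be read as a delirium association at all, in a study whose stated aim is to isolate that association.

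**Working it through.** **Inputs from the article:** two ICUs; type I error 5% (sidedness not stated, two-sided assumed); 2-point difference; 80% power; 81 per group.

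**Not in the article, so assumed and shown as a range:** the SD, the site split, the delirium rate at each site, and the outcome difference between sites, *d*.

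**Step 1: the plan's own figure.** No SD is stated, so 81 cannot be reproduced independently. Solving n = 2(1.960 + 0.842)² SD² / 2² for n = 81 gives SD = 2 × √(81/2) / 2.802 = 4.54. The noncentral *t* version gives 4.52. An SD of about 4.5 is therefore what the stated sample size implies.

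**Step 2: distortion in a pooled comparison.** With site A holding half of the patients,

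bias = *d* × [P(site A | delirium-positive) – P(site A | delirium-negative)].

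- Rates 60% v 40%: 0.60/1.00 – 0.40/1.00 = 0.20
- Rates 70% v 30%: 0.70/1.00 – 0.30/1.00 = 0.40
- Rates 80% v 40%: 0.80/1.20 – 0.20/0.80 = 0.667 – 0.250 = 0.417

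**Step 3: false-positive rate.** This is Φ(–1.96 – bias/SE) + Φ(bias/SE – 1.96), with SE = 4.54 × √(1/n₁ + 1/n₂). For 81 v 81, SE = 0.714. At 80% v 40%, 162 patients split about 97 v 65, and SE = 0.728.

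| Delirium rates | *d* = 0 | *d* = 1 | *d* = 2 |
|---|---|---|---|
| Equal | 0; 5.0% | 0; 5.0% | 0; 5.0% |
| 60% v 40% | 0; 5.0% | 0.20; 5.9% | 0.40; 8.7% |
| 70% v 30% | 0; 5.0% | 0.40; 8.7% | 0.80; 20.2% |
| 80% v 40% | 0; 5.0% | 0.42; 8.8% | 0.83; 20.8% |

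Each cell gives the bias in MMSE points, then the two-sided false-positive rate. The largest bias, 0.83, is about 42% of the 2-point target. An unequal site split weakens it: with 70% of patients at site A, rates of 70% v 30% and *d* = 2, the bias is 0.69 and the false-positive rate 16.2%.

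**Step 4: price of adjusting.** With equal site sizes and equal delirium groups, adding site inflates the variance of the delirium effect by 1/(1 – φ²), where φ is the difference in delirium rates.

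- Equal rates: factor 1, 81 per group.
- 60% v 40%: 1/(1 – 0.04) = 1.042; 81 × 1.042 = 84.4, so 85 per group. Power at 81 is 78.4%.
- 70% v 30%: 1/(1 – 0.16) = 1.190; 81 × 1.190 = 96.4, so 97 per group. Power at 81 is 72.8%.

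This takes no credit for any residual variance that site explains.

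**The case against.** The strongest reply is that the same section already lists ANCOVA and confounder regression, both of which can hold site, and that a condensed article may leave the covariate list to a fuller plan. This stands in part: the absence of a covariate list is not the complaint. But the article does commit to particular tests for the group comparisons, and those tests are unadjusted. ANCOVA is optional and the regression is supplementary.

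It is also fair that both sites use the same instruments as standard care, and that the primary outcome in the Sample Size section is a decrement. A site that scored consistently more strictly at both time points would largely cancel out of a change score. A real difference between sites in the course of recovery would not.

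Three stronger readings are tempting but unsupported:

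- *Each ICU's own staff score cognition, so site shapes the measurement of both exposure and outcome.* The article does not say who administers or scores the MMSE or TICS. Follow-up TICS is by telephone, possibly by one central caller. The IES-R goes by mail to the patient and the IQCODE to the person responsible.
- *A site effect does bias the result.* Bias needs a difference in delirium rate and a difference in outcome level together. The article documents neither.
- *Site is not recorded, because Textbox 1 omits it.* The enrolling hospital is known for every patient from recruitment.

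**Conclusion.** The point holds as a weakness in the choice of main tests: two ICUs are pooled, exposure is unrandomised and labelled locally, and the committed comparisons cannot separate site from delirium. It is not evidence that the result will be biased.

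The size is unknown. The range of 0 to about 0.8 MMSE points rests on equal-sized sites, the back-solved SD and assumed site contrasts. The upper end needs a 40-percentage-point gap in delirium rates and a site difference as large as the whole clinical target. The milder case (60% v 40%, 1 point) costs 0.20 points and a false-positive rate of 5.9%, close to nominal. The importance is moderate: the change is worth making because the alternative is better suited and cheap, not because a large error has been shown.

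**What to change.** State in Statistical Analysis that the main group comparisons are adjusted for site:

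- for means, the ANCOVA or multiple regression already listed, with delirium group and site as terms, in place of the *t* test;
- for the non-parametric route, the van Elteren (site-stratified Wilcoxon) test in place of Mann-Whitney;
- for proportions, including mortality, Cochran-Mantel-Haenszel stratified by site in place of chi-square.

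Report the delirium rate and the group difference separately for each ICU, so that readers can see whether site mattered.

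**Cost:** no new data, a sentence or two of text, and one degree of freedom. If delirium rates differ by site there is also some loss of precision: about 85 per group instead of 81 for 80% power at 60% v 40%, and 97 at 70% v 30%. That loss arises only where there is imbalance to correct.

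**Limit:** site adjustment removes between-site confounding only. It does not repair misclassification of delirium within a site, and it does not replace adjustment for patient-level confounders.

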## Introduction

Delirium is a disturbance of consciousness, developed over a short period of time, where inattention is accompanied by a change in cognition and/or perceptual disturbance [1]. Delirium occurs in a variety of health care settings [2] and affects between 15% to 20% of general hospital patients [3,4], including as many as 80% of critically ill, intensive care unit (ICU) patients receiving mechanical ventilation [5].

In the ICU, delirium is associated with critical illness itself, particularly with multiple comorbidities and multi-organ failure, as well as management-related factors such as mechanical ventilation, sedation, and lack of sleep [2,6,7]. Delirium is also associated with adverse outcomes including death and long-term cognitive impairments [7-9], and potentially traumatic stress symptomatology. Several studies suggest delirium-related risks are cumulative and may foster the development of cognitive dysfunction, poorer functional status, and impair quality of life [7-23]. Despite literature reports of a reduced quality of life for survivors of critical illness and delirium in the ICU, the long-term follow-up of cognitive and psychosocial function still remains relatively unexplored. This study will address this by following up with patients for one year after discharge from the ICU. We will employ a set of tests that complement each other [24] in order to create a comprehensive view of a patient's cognition and psychosocial well-being at 12 months after leaving the ICU. These tests assess cognition and evidence of post-traumatic stress disorder (PTSD) [25], while also using each patients “person responsible” to assess their relative's and/or friend’s psychosocial function at 12 months after their discharge from the ICU in comparison to their pre-ICU psychosocial abilities. This study is expected to provide novel insight into the cognitive and psychosocial impact of ICU mechanical ventilation-related delirium and to assist in improving the care of critically ill intensive care patients by highlighting the importance of the need to monitor for the development of delirium.

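### The two-group comparison of means uses the Student t test conditioned only on normality, although group sizes are not controlled; naming the Welch version is a cheap safeguard if sizes and SDs both differ.

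*Protocol article*

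**What the plan says.** All points are in the protocol article.

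- **Test (Statistical Analysis).** The text reads "We plan to employ the Student" t test, "to compare mean outcomes in each group when assuming a normal underlying distribution can be justified". The alternative is the Mann-Whitney U "test to compare medians when this assumption fails". The decision rule looks at distributional shape; variances are not mentioned.
- **Reporting (Statistical Analysis).** "Results will be presented as differences between groups with 95% confidence intervals".
- **Other analyses (Statistical Analysis).** "We will also consider both analysis of covariance (parametric) or Kruskal-Wallis (non-parametric) testing as appropriate", plus regression to examine confounders.
- **Group formation (Methods, before Participants).** A patient with any positive CAM-ICU is delirium-positive. One who never tests positive while ventilated is delirium-negative. No quota per group is stated.
- **Expected share (Introduction).** Delirium affects a range of patients, "including as many as 80% of critically ill, intensive care unit (ICU) patients receiving mechanical ventilation".
- **Sample size (Sample Size).** At least 81 patients per group, 200 enrolled, 80% power, "at a type 1 error rate of 5% (alpha .05"), for a difference of 2 MMSE points. No SD and no expected split are given.

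**The concern.** The Student t test, as the name is usually understood, pools the two sample variances. With equal group sizes this does little harm even when the SDs differ. With unequal sizes the pooled standard error is weighted towards the larger group's variance, whereas the true standard error is driven mainly by the smaller group's. The test is then miscalibrated unless the two SDs agree.

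This design does not secure equal sizes, because observed CAM-ICU results decide who is in which group. The planned fallback does not help: Mann-Whitney is triggered by non-normality, so roughly normal data with different spreads would still go to the pooled test. At stake are the P values and the 95% confidence intervals that the plan promises for group differences.

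**Working it through.** **The plan's own figure.** The SD behind 81 per group is not stated, so the figure can only be back-solved. From n = 2(1.96 + 0.84)²·SD²/δ² with n = 81 and δ = 2, SD = (2/2.80)·√(81/2) ≈ 4.54 (4.52 using the t distribution). The 81 is therefore consistent with a two-sided, 1:1, common-SD calculation, but it is not independently reproduced. Sidedness is not stated; two-sided is assumed.

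**Inputs.**
- From the protocol: δ = 2, alpha 5%, 81 per group, 200 enrolled, delirium in up to 80%.
- Assumed: all SDs, the splits, normal data, and 162 completers in the 80:20 case (162/200 corresponds to 19% loss).
- Splits tried: 81/81 is the planned minimum. 119/81 is the most unequal split of 200 that still meets that minimum (200 − 81 = 119, or 59.5% delirious with no dropout). 130/32 is 80:20 of 162 (0.8 × 162 ≈ 130).
- SDs and sizes are given as delirium-positive v negative.

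**Formulas.**
- Pooled variance: s_p² = [(n₁−1)s₁² + (n₂−1)s₂²]/(n₁+n₂−2)
- Standard error the test uses: SE_p = √[s_p²(1/n₁ + 1/n₂)]
- True standard error: SE = √(s₁²/n₁ + s₂²/n₂)
- With r = SE_p/SE and critical value t_c, type I error ≈ 2[1 − Φ(t_c·r)] and power ≈ Φ(δ/SE − t_c·r)

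**81/81.** When n₁ = n₂, both standard errors reduce to √[(s₁²+s₂²)/n], so r = 1. Simulation gave a pooled type I error of 5.0% at every SD ratio from 0.5 to 2.

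**119/81, SD 6 v 4.** s_p² = (118×36 + 80×16)/198 = 27.9. SE_p = 0.761, SE = √(36/119 + 16/81) = 0.707, r = 1.076. Type I error ≈ 2[1 − Φ(1.972×1.076)] = 3.4%. Simulated power is 75.9% pooled and 80.3% Welch.

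**119/81, SD 4 v 5.** s_p² = (118×16 + 80×25)/198 = 19.6. SE_p = 0.638, SE = 0.666, r = 0.959. Type I error ≈ 5.9%; simulation gives 6.0%.

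**130/32, SD 6 v 4.** s_p² = (129×36 + 31×16)/160 = 32.1. SE_p = 1.118, SE = √(36/130 + 16/32) = 0.881, r = 1.269. Type I error ≈ 2[1 − Φ(1.975×1.269)] = 1.2%; simulation gives 1.3%. Power ≈ Φ(2/0.881 − 2.506) = 41%, against 61% for Welch.

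**130/32, SD 4 v 5.** s_p² = (129×16 + 31×25)/160 = 17.7. SE_p = 0.831, SE = 0.951, r = 0.874. Type I error ≈ 8.4%; simulation gives about 8.5%, and the nominal 95% interval covers about 91%.

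**Equal SDs.** Then r = 1 on average whatever the split, and the pooled test holds 5% even at 160/40.

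| Split | SDs | Pooled type I error | Welch type I error |
|---|---|---|---|
| 81/81 | any ratio 0.5–2 | 5.0% | about 5% |
| 119/81 | 6 v 4 | 3.4% | about 5% |
| 119/81 | 4 v 5 | 6.0% | about 5% |
| 130/32 | 6 v 4 | 1.3% | about 5% |
| 130/32 | 4 v 5 | about 8.5% | about 5% |

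**Cost of Welch with equal SDs of 4.5 (simulated power, pooled v Welch).** 80.3% v 80.3% at 81/81; 73.3% v 72.9% at 113/49; 70.6% v 69.6% at 160/40; 60.8% v 59.6% at 130/32.

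**The case against.** The strongest reply is that a condensed article may use the Student name for the two-sample t test in general, and that the choice of variant belongs in the analysis plan. The text does not say pooled or equal-variance; that reading rests on the usual meaning of the name. This lowers the severity but does not remove the point, because the article names a test and states the condition for using it, and that condition omits variance.

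Four further objections stand and limit the claim:

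- **No SDs are given.** A reader might infer that the P values and intervals are wrong whenever the SDs differ. At 81/81 they are not. A reader might also infer that delirium-positive patients vary more. A ceiling on the 0–30 MMSE makes that plausible, but no figure in the protocol shows it. If it is so and they are the larger group, the error is conservative, and the false-positive scenario needs the opposite ordering.
- **The 80% is an upper figure from the literature.** It is not a forecast for this cohort, from which nursing home residents and patients with evident decline are excluded. That the groups will be very unequal does not follow. The 130/32 case also breaks the protocol's own minimum; at 119/81, which respects it, the effects are modest.
- **Imbalance costs power under either test.** With equal SDs of 4.5, power falls from 80% at 81/81 to about 61% (pooled) or 60% (Welch) at 130/32. That is a sample-size matter.
- **The t test may not be used.** If normality is judged to fail, Mann-Whitney replaces it. The calculations here assume normal data.

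**Conclusion.** The point holds as a minor, cheap improvement. The protocol names the Student t test with normality as its only condition, in a design that does not fix group sizes. Miscalibration requires unequal sizes and unequal SDs together; either alone leaves the type I error at 5%.

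Under the assumed SDs, the pooled type I error runs from 3.4% to 6.0% at the most unequal split that meets the planned minimum, and from 1.3% to about 8.5% at 80:20 of 162 completers. In the SD 6 v 4 case at 130/32, the pooled test gives up about 20 points of power relative to Welch (41% v 61%). The mechanism is certain. Its size and direction in this cohort are unknown, because the documents give neither SDs nor an expected split.

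**What to change.** In Statistical Analysis, replace the Student t test with the Welch (unequal-variance) t test for all two-group comparisons of means, and state that the 95% confidence intervals come from the same method. Fixing this before analysis also avoids choosing between two reported results afterwards.

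The change is one phrase. With equal SDs it loses nothing at 81/81 and about 1 point of power at 80:20 (1.2 points at 130/32). Heteroscedasticity-robust standard errors in the adjusted linear models would be consistent with it but are optional. The power lost if one group falls well below 81 needs separate attention; this change does not address it.

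### The 30 + 30 cross-validation is, as written, an underpowered nested subset of the study's own patients with no stability criterion, so it cannot serve as validation

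*Protocol article*

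**What the plan says.** The last sentence of the Statistical Analysis section of the protocol article states that "we will randomly select two groups of patients (30 delirium-positive and 30 delirium-negative) to cross validate our results". A second aim is named for the same draw: to "assess whether they are stable for both samples". The sentence follows directly on the plan to examine confounders by regression. The section does not say that the 60 patients are kept out of the main analysis, that a model is fitted in one part and tested in another, or what result would count as stable.

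The Sample Size section sets the scale of the study. Its target is "the clinically significant difference of 2 points on the MMSE between groups". For 80% power it requires at least 81 delirious and 81 non-delirious patients. On enrolment it says: "To allow for potential dropouts following recruitment, we plan to enroll 200 patients". No other cohort appears anywhere in the article. No power or precision is given for the 30 + 30 comparison.

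**The concern.** Cross-validation means estimating on one set of patients and checking on patients who did not contribute to that estimate. Here the check appears to reuse patients who already contributed. Agreement is then partly built in, because the subset carries some of the same random error as the full sample. Disagreement is mostly a product of the smaller number.

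The check could therefore mislead in two ways. A real difference may be described as unstable because 60 patients are too few to show it. A chance finding may gain apparent support from its own data. With no criterion fixed in advance, the outcome of a single random draw can be described either way.

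**Working it through.** **Inputs.** From the Sample Size section: difference 2 points, alpha .05, power 80%, 81 per group, 200 enrolled. From the Statistical Analysis section: 30 per group in the check. Assumptions: two-sided test, normal outcome, and a standard deviation back-solved because none is stated.

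**Implied standard deviation.** From n = 2σ²(1.960 + 0.842)²/δ², with n = 81 and δ = 2:
- σ = 2 / (2.802 × √(2/81)) = 4.54. The exact t test gives 4.52, and a one-sided test would give 5.12.
- Putting 4.54 back: 2 × 20.61 × 7.85 / 4 = 80.9, which rounds up to 81. This is circular by construction. The 81 cannot be verified independently.

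**Power at 30 per group.** The standard deviation cancels, since 81 per group with 80% power fixes the effect-to-SD ratio:
- 2.802 × √(30/81) = 1.705, and Φ(1.705 − 1.960) = 0.40. The exact t test gives 0.39.
- Variants: 45% one-sided, and 30% at alpha .025 (Bonferroni over two time points).
- Difference detectable with 80% power: 2.802 × 4.54 × √(2/30) = 3.3 points.

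**Precision.** The 95% half-width at 30 per group is 2.00 × 4.52 × √(2/30) = 2.3 points, more than the 2-point difference. At 81 per group it is about 1.4. Unlike power, these figures depend on the assumed standard deviation.

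**Nested subset.** In theory the full-sample and subset estimates correlate at √(30/81) = 0.61, or √(30/100) = 0.55 with 100 per group. Trials were simulated with a t test at .05 and a random 30 + 30 drawn from within each. Stability was taken to mean P<.05 in the same direction, which is an assumption.

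| Full sample | True 2-point difference, full result significant: subset fails to repeat | Same: sign reverses | No true difference, full result falsely significant: subset confirms |
|---|---|---|---|
| 81 / 81 | about 53% | about 1.5% | about 25% |
| 100 / 100 | about 56% | about 2.4% | about 21% |
| 130 / 32 | about 42% | under 1% | about 38% |

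An independent sample would confirm a false positive in the same direction 2.5% of the time. The 130/32 row takes 162 evaluable patients (2 × 81) and 80% delirium: 0.80 × 162 = 130, leaving 32. The Introduction gives 80% as an upper figure, so this row is an extreme. Drawing 30 of 32 then uses nearly the whole delirium-negative group, which raises agreement for true and false findings alike.

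**Hold-out reading.** If the 60 were kept out, the main analysis would have 81 − 30 = 51 per group (60% power), or 100 − 30 = 70 per group with no dropout (74% power). The check itself would be independent but would still have about 39% power.

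**The case against.** The strongest defence is that the article never ties stability to P<.05. The same section promises differences with 95% confidence intervals, and judged by the estimate the subset nearly always agrees: its sign reverses in only about 2% of significant trials with balanced groups. A reader might infer that the check will contradict a true finding more often than not. The documents do not support that. A non-significant subset is not a contradiction, the significance rule is supplied by the reader, and in the 130/32 case the subset repeats the result in about 58% of trials even under that rule. With a true difference above about 2.3 points, power at 30 per group passes 50%.

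It is also fair to say that a condensed article may omit detail, that a split-sample check of the regression models is not excluded, and that no decision rule hangs on this step. A reader might infer that the check validates nothing at all; that too goes further than the text, which leaves the hold-out question open.

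These points limit the claim but do not remove it. The size and manner of the draw are stated, not left to another document. Easy agreement of the estimate is what overlap produces, so it is weak evidence of stability. The hold-out reading makes the check independent only by taking the main analysis below the study's own stated minimum.

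**Conclusion.** The concern holds in limited form. As described, the 30 + 30 step is a nested subset with about 39% power at the planned difference and no criterion for stability, and it should not be called cross-validation. The power figure follows from the protocol's own sample size under a two-sided test. The ±2.3-point interval rests on the implied standard deviation of about 4.5. The failure and false-confirmation rates also assume that agreement is judged at P<.05 and that the true difference is 2 points or nil.

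The failure rate is not above one half in every case: it is about 53% to 56% with balanced groups and about 42% at the imbalanced extreme. On the nested reading the primary comparison is unaffected; what would mislead is the planned statement about stability. On the hold-out reading the primary comparison itself would lose power.

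**What to change.** Delete the 30 + 30 step and the description of it as cross-validation. Report the primary difference on all patients with a bootstrap confidence interval, resampling within group and site. If a regression model is to be validated, use k-fold cross-validation or bootstrap optimism correction on all patients, and state beforehand which performance measure will be reported. Estimates for each of the two sites may be shown descriptively only, since they are again small subsets.

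The bootstrap also reuses the study's data. It describes sampling variability and is no substitute for an external cohort, so the report should not claim validated results. The change needs no further patients or data: it costs a wording amendment and a little more analysis work.
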